### Assignment of interventions: blinding

#### Who will be blinded {17a}

Consistent with a double-blinded design, all participants, investigators, and study staff who have a role in promoting adherence or assessing or documenting outcomes are blinded to the treatment assignment. During the main part of the trial, only the statistician responsible for generating the randomization scheme and the compounding pharmacy have access to the treatment assignment information. Study-wide unblinding will take place when data from all trial data forms and measurements have been entered into the study database for all participants, data cleaning for the trial has been completed, the data have been locked, and the principal investigator has declared the study dataset to be complete.

#### Procedure for unblinding if needed {17b}

Unblinding prior to the study-wide unblinding date will be undertaken only in exceptional circumstances in which knowledge of a participant’s actual intervention assignment is essential to protect the safety of a participant or another individual. Examples include the occurrence of a serious adverse event for which knowledge of the participant’s assignment could affect her immediate care or consumption of study drug in excessive or toxic quantity by the participant or by another party. The decision to unblind will be made on a case-by-case basis by the principal investigator, in consultation with the Steering Committee or DSMB as needed, and knowledge of treatment assignment will be restricted to the smallest number of people possible. If the decision to unblind a participant is made, an analyst who is not otherwise involved in collecting, cleaning, or interpreting trial data will consult the list of randomization numbers to access treatment assignment information for the participant’s randomization number, documenting the date and reason for unblinding. Treatment assignment will be revealed for the relevant individual participant only, so that unblinding of one participant does not compromise the blinding of other participants.

### Data collection and management

#### Plans for assessment and collection of outcomes {18a}

Cognitive function outcomes will be assessed using a battery of neuropsychological tests (see the “Outcomes {12}” section) administered by clinical research coordinators who have completed dedicated training and certification by a neuropsychiatry or neuropsychologist investigator, who will also oversee the quality of these assessments. Whenever possible, repeated cognitive measures in the same participant will be administered by the same evaluator and use the same mode of administration (in person versus by video visit) across all study time points. Additionally, a sample of session recordings will be observed by the neuropsychologist co-investigator to ensure standardized administration across coordinators.

Frequency and type of incontinence will be assessed using a standardized, 7-day voiding diary. At baseline and outcome follow-up visits, participants will receive a blank diary and instructions on using it to record each time they leak urine as well as indicate whether the leakage is associated with a sudden or strong urge to urinate. Diary data will be abstracted by blinded analysts who have undergone study-specific training and supervised practice in reviewing and abstracting diary data to calculate the frequency of incontinence associated with urgency.

Structured self-report questionnaires will be used to assess other urinary, sleep-related, perceived physical function, psychological, and bowel function outcomes (see the “Outcomes {12}” section). Participants may complete the questionnaires electronically or alternately complete them on paper and then return them to blinded study coordinators for electronic data entry.

Physical performance and balance testing will be performed by clinical research coordinators who have completed study-specific training in these measures. Testing will be performed in person or through video-based visits, following procedures outlined in the study manual of operations, but the same mode of assessment will be preferentially used at baseline and follow-up assessments.

#### Plans to promote participant retention and complete follow-up {18b}

To promote retention and follow-up, participants are offered multiple methods of completing follow-up visits and measures. Cognitive and physical function assessments can be completed in person in a study clinic or via videoconference-based study visits. Study questionnaires can be completed on paper or online, either in a study clinic or at home. Participants receive reimbursement for their time and trouble completing study follow-up visits and measures. Participants are encouraged to complete all study outcome and safety monitoring measures even if they discontinue study interventions early.

#### Data management {19}

Study data are electronically entered, managed, and edited by clinical coordinators or other study staff using the Medrio web-based Electronic Data Capture software for Clinical Research, a secure, 21 Code of Federal Regulations Part 11 compliant web-based application designed for research data entry and management. The Medrio system automatically generates queries for missing data or out-of-range values based on initial programming by analysts at the UCSF Data Coordinating Center. As described in the Data and Safety Monitoring Plan (DSMP), the UCSF Data Coordinating Center under the supervision of the principal investigator provides a secondary layer of oversight for data accuracy and completeness by tracking data queries posted in the electronic data capture system, prompting site-specific study personnel to address data queries for missing or out-of-range data in a timely manner, and generating study-wide reports for reviews of missing data or data outliers. Overall data completeness and quality are periodically assessed by the UCSF Data Coordinating Center using measures such as number of missing data forms and number of outstanding data queries flagged within this system.

#### Confidentiality {27}

All study-related information is stored securely at the study site or using secure electronic platforms. All paper-based participant information is stored in locked file cabinets in research facilities with limited access. All data collection, process, and administrative forms are identified by a coded participant ID (identification) number only to maintain participant confidentiality. All records that contain names or other personal identifiers, such as informed consent forms, are stored separately from study records identified by code number. All local databases are secured with password-protected access systems with dual-factor authentication. Forms, lists, logbooks, appointment books, and any other listings that link participant ID numbers to other identifying information are stored in a separate, locked file in research facilities with limited access. Participants’ study information will not be released outside of the study without the written permission of the participant, except as necessary for monitoring by the sponsor and/or its contractors or by government or regulatory authorities.

#### Plans for collection, laboratory evaluation, and storage of biological specimens for genetic or molecular analysis in this trial/future use {33}

Not applicable—the TRIUMPH trial does not include any plans for collection, laboratory evaluation, or storage of biological specimens.

## Statistical methods

### Statistical methods for primary and secondary outcomes {20a}

To examine the primary outcome, medication effects on cognitive function will be estimated using a linear mixed model (LMM) for repeated changes from the baseline of the composite cognitive function outcome, averaged at 4, 12, and 24 weeks, adjusted for baseline value. In addition to a fixed effect for study location, the LMM will include terms for time (as a categorical variable) and time-by-treatment interactions. Treatment effects will be captured by the time-by-treatment interactions and their 95% confidence intervals, focusing on the comparisons of the anticholinergic arm with each of the two other arms.

The primary hypothesis will be tested using the average of the time-by-treatment interactions at 4, 12, and 24 weeks. Persistence of treatment effects will be evaluated by examining the time-by-treatment interaction at 36 weeks, and second by contrasting the 36-week interaction with the average of the 4-, 12-, and 24-week interactions, which will capture attenuation of the on-treatment effect after an additional 12 weeks. In models involving the average of the effects at 4, 12, and 24 weeks, we will check for heterogeneity and trend across those visits. If evidence of heterogeneity is detected, we will consider examining time-by-treatment interactions at each time point (4, 12, and 24 weeks) separately.

The primary analyses will be by intention to treat among participants with at least one post-baseline follow-up assessment, according to treatment group assignment, and without regard to adherence, avoiding selection bias from informative discontinuation of treatment. However, secondary per-protocol analyses omitting those outcomes will also be performed, since the inclusion of post-discontinuation outcomes may attenuate treatment effect estimates if treatment effects are primarily acute.

For secondary outcomes, treatment effects will also be estimated using similar LMMs based on change from baseline in measures at 4, 12, 24, and 36 weeks, adjusted for baseline values of outcomes. Once again, treatment effects will be captured by the time-by-treatment interactions and their 95% confidence intervals, focusing on the comparisons of the anticholinergic arm with each of the two other arms. Analyses will again be by intention to treat, according to treatment group assignment, and without regard to adherence; per-protocol analyses, as described above for the primary outcome, will also be performed for secondary outcomes. The study team will again examine the average of the time-by-treatment interactions at 4, 12, and 24 weeks, while checking for heterogeneity and trend across those visits, and then contrast the 36-week interactions with the average of the 4-, 12-, and 24-week interactions. No penalization for multiple comparisons will be made, but the results will be presented as secondary outcome analyses.

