### Sample size {14}

A sample size of 270 participants, randomized in equal proportions to the three arms, has been chosen to provide > 80% power in 2-sided tests with an experiment-wise type 1 error rate of 5%, corrected for two comparisons (anticholinergic therapy to beta-3-adrenergic agonist therapy; anticholinergic therapy to placebo) [48] to detect an average treatment effect of 0.25 standard deviation’s difference in the composite cognitive function outcome over 6 months, assuming an intraclass correlation of 0.75 among repeated cognitive outcomes, and cumulative loss to follow-up level of 15% by 6 months of treatment.

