### Methods for additional analyses (e.g., subgroup analyses) {20b}

Intervention effects will be analyzed in subgroups in multivariate analyses based on a limited set of clinicopathologic factors that are hypothesized to have the potential to influence intervention effects. For all outcomes, the investigators will explore whether participant age (< 75 vs. ≥ 75 years) modifies the effects of treatment, unless this is precluded by a minimal subgroup sample size. Other pre-specified subgroup analyses include the following:Baseline cognitive function status (MoCA score < 26 vs. ≥ 26–30) for cognitive function outcomesBaseline frequency of incontinence (daily vs. less than daily incontinence), for urinary symptom outcomesBaseline global physical performance (SPPB score < 10 vs. ≥ 10), for physical function or performance outcomesBaseline poor sleep quality (PSQI score > 5 vs. ≤ 5), for sleep-related outcomesBaseline depression (GDS-15 ≥ 9 vs. < 9) or anxiety (GAD-7 ≥ 10 vs. < 10) symptom score, for depression or anxiety outcomes, respectively

Subgroup-specific effects will be presented only if the interaction between treatment and subgroup is statistically significant at *p* < 0.05.

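### The cognitive models could gain modest precision at almost no cost by also adjusting for screening MoCA and age (an optional improvement, not an error)

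*Protocol article*

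**What the plan says.** Under Statistical methods {20a}, the primary analysis models change in the composite at weeks 4, 12 and 24, adjusted for its baseline value. The other terms are these: "In addition to a fixed effect for study location, the LMM will include terms for time (as a categorical variable) and time-by-treatment interactions". Secondary outcomes, including each single cognitive test, use similar models "adjusted for baseline values of outcomes".

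MoCA is scored at screening, because a low score excludes a woman (Exclusion criteria). Age is an inclusion criterion. In the analysis both appear only as cut-point subgroup factors under Methods for additional analyses {20b}: "the investigators will explore whether participant age" modifies the effects, and MoCA is split at 26 for the cognitive outcomes.

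Under Outcomes {12}, the composite at each visit is the average Z score of all tests completed at that visit.

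The Sample size section {14} gives "A sample size of 270 participants, randomized in equal proportions to the three arms", with "> 80% power in 2-sided tests" and an "experiment-wise type 1 error rate of 5%, corrected for two comparisons". The aim is "to detect an average treatment effect of 0.25 standard deviation’s difference in the composite cognitive function outcome over 6 months". The calculation takes the ICC of the repeated cognitive measures as 0.75 and allows for 15% cumulative loss by 6 months.

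**The concern.** With an ICC of 0.75, one baseline composite is a good but imperfect measure of a woman's stable cognition, and some stable between-woman variation stays in the residual. A second cognitive measure from a separate occasion (screening may precede baseline by up to 60 days) can pick up part of it, and age may pick up more. In a randomised comparison, adjusting for such pre-randomisation variables does not bias the treatment contrast.

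What is at stake is the width of the confidence intervals. This matters because the power target is met with little to spare, and because a null result will be read by how much cognitive harm the interval excludes.

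**Working it through.** **Inputs.** From Sample size {14}: 90 women per arm, difference 0.25 SD, ICC 0.75, 15% loss by week 24, 5% error over two comparisons. Assumptions of mine: Bonferroni (two-sided 0.025 each, critical value 2.2414), compound symmetry that includes baseline, and SD 1 for the composite at one visit.

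**1. Residual variance of the three-visit mean, given own baseline.**

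- Unadjusted: (1 + 2 × 0.75)/3 = 0.8333.
- Adjusted: 0.8333 − 0.75² = 0.2708, a 67% reduction.
- Stable between-woman part of what is left: 0.75 × (1 − 0.75) = 0.1875, or 69% of 0.2708. This is the ceiling on what further baseline covariates could remove.

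**2. The plan's power.** Power = Φ(0.25/SE − 2.2414).

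| Loss pattern | SE | Power |
|---|---|---|
| None: √(2 × 0.2708/90) | 0.0776 | 83.7% |
| 5/10/15% at weeks 4/12/24 (mixed-model information) | 0.0808 | 80.4% |
| All 15% after week 12 | 0.0785 | 82.7% |
| All 15% before week 4: √(2 × 0.2708/76.5) | 0.0841 | 76.7% |

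The stated power is therefore reproduced without extra covariates when loss is gradual.

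**3. Adding MoCA to the primary model.** Suppose MoCA correlates r with the composite at every visit and has its own independent error. Given baseline, its covariance with the follow-up mean is r − 0.75r = 0.25r, and its own residual variance is 1 − r². The variance removed is (0.25r)²/(1 − r²). The documents give no r. I take correlations of 0.4 to 0.7 with true cognition, multiplied by √0.75.

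| r (assumed) | Variance removed | Share of 0.2708 | Fall in contrast variance, 5/10/15% loss | Power |
|---|---|---|---|---|
| 0.35 | 0.0085 | 3.1% | 3% | 81.7% |
| 0.43 | 0.0144 | 5.3% | 5% | 82.6% |
| 0.52 | 0.0231 | 8.5% | 8% | 84.0% |
| 0.61 | 0.0363 | 13.4% | 13% | 86.0% |

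Entry is limited to MoCA 18 to 30, which narrows its spread and favours the lower half of the table. Any contribution from age is not included.

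**4. Cost in degrees of freedom.** With about 230 women (270 × 0.85 = 229.5) and six existing parameters, two more covariates inflate the variance by 224/222 = 1.009, about 1%. At r = 0.35 the contrast variance becomes 0.00652 × 0.969 × 1.009 = 0.00638, SE 0.0799, power 81.3%.

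**5. Single-test models.** There are six test scores, so five others for each. Let c be the correlation between tests, the same within and across visits. The mean of the other five has variance (1 + 4c)/5. Given the test's own baseline, the variance removed is (c − ICC × c)²/((1 + 4c)/5 − c²). The residual variance before the addition is ICC + (1 − ICC)/3 − ICC²: 0.2708 at ICC 0.75 and 0.3733 at ICC 0.6.

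| c (assumed) | ICC 0.75 | ICC 0.6 |
|---|---|---|
| 0.25 | 0.0116/0.2708 = 4% | 0.0296/0.3733 = 8% |
| 0.35 | 0.0214/0.2708 = 8% | 0.0548/0.3733 = 15% |
| 0.45 | 0.0354/0.2708 = 13% | 0.0906/0.3733 = 24% |

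The plan gives 0.75 for repeated cognitive outcomes. A lower value for a single test is plausible but is not in the documents.

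**The case against.** The strongest reply is that nothing here is wrong. The model adjusts for the outcome's baseline and for site, the only stratification factor. It is unbiased, and own-baseline adjustment already takes out 67% of the variance of the visit mean. The article condenses a fuller protocol, and an analysis plan that is not shown may add covariates. All of this stands, and it is why the point is a suggestion. It is still worth making, because the article names the model's terms and these two variables are not among them.

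Three stronger readings are tempting, and the documents do not support them.

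- *The primary model ignores the other baseline tests.* It does not: the baseline composite is their average. That remark applies only to the single-test models, which are secondary, carry no power claim and have no multiplicity control.
- *The trial is underpowered without these covariates.* The 76.7% figure needs all 15% of losses to fall before week 4, which is not the natural reading of a cumulative loss by 6 months.
- *Naming MoCA and age as subgroup factors makes their absence from the main model inconsistent.* Exploring effect modification and gaining precision are different purposes, so there is no contradiction.

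It is also fair to say that a weakly related covariate could gain nothing once degrees of freedom are paid for.

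**Conclusion.** The point holds as an optional efficiency gain. For the primary outcome the likely benefit is about 1 to 2 percentage points of power per comparison (80.4% to 81.7–82.6%), slightly less after degrees of freedom; the top of the assumed range, 86.0%, needs a MoCA correlation of 0.61. For single tests the saving in residual variance is 4 to 13% at the plan's ICC, or 8 to 24% if single tests are as noisy as ICC 0.6.

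These sizes rest on compound symmetry, independent measurement error, a Bonferroni split, and correlations that the documents do not supply. A reader should not infer that the plan's analysis is invalid or its power statement false.

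**What to change.** In Statistical methods {20a}, add screening MoCA and age, both continuous, as fixed covariates in the primary model. Do the same in each single-test cognitive model, and there also add the baseline mean Z score of the other tests. The primary model does not need that last term. State the list before study-wide unblinding and leave the treatment contrasts as they are. If the full analysis plan already names these covariates, it is enough to align the published description.

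The cost is one or two sentences and about two degrees of freedom in the primary model (three in each single-test model). No new data, visits or participants are needed, and MoCA should be complete because it is required for eligibility.

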### Interim analyses {21b}

This trial focuses on medications that are already in widespread use in the community for urgent incontinence and administers these medications according to their already FDA-approved indications and designated populations. The trial is designed to follow participants for limited time periods (24 weeks of medication treatment, as well as 12 weeks after discontinuation of treatment), using self-report measures and other non-invasive data collection procedures that impose only a modest burden on participants. As a result, the investigators do not believe there is a compelling scientific or ethical rationale to stop the trial earlier than planned even if differences in the trial’s cognitive, urinary, or functional outcomes begin to emerge earlier than expected. Early termination of the trial based on preliminary data trends could increase the risk of spurious conclusions and endanger the credibility of the findings in the broader clinical community, especially given that many clinicians may have strong preferences or biases related to these medications. Therefore, no interim treatment analyses for the trial’s cognitive, urinary, or other functional outcomes are planned in advance.

### Methods for additional analyses (e.g., subgroup analyses) {20b}

Intervention effects will be analyzed in subgroups in multivariate analyses based on a limited set of clinicopathologic factors that are hypothesized to have the potential to influence intervention effects. For all outcomes, the investigators will explore whether participant age (< 75 vs. ≥ 75 years) modifies the effects of treatment, unless this is precluded by a minimal subgroup sample size. Other pre-specified subgroup analyses include the following:Baseline cognitive function status (MoCA score < 26 vs. ≥ 26–30) for cognitive function outcomesBaseline frequency of incontinence (daily vs. less than daily incontinence), for urinary symptom outcomesBaseline global physical performance (SPPB score < 10 vs. ≥ 10), for physical function or performance outcomesBaseline poor sleep quality (PSQI score > 5 vs. ≤ 5), for sleep-related outcomesBaseline depression (GDS-15 ≥ 9 vs. < 9) or anxiety (GAD-7 ≥ 10 vs. < 10) symptom score, for depression or anxiety outcomes, respectively

Subgroup-specific effects will be presented only if the interaction between treatment and subgroup is statistically significant at *p* < 0.05.

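### All seven prespecified effect modifiers are tested only as two groups, which wastes information if modification is graded; the depression and anxiety cuts may also leave few women per arm

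*Protocol article*

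**What the plan says.** The section on additional analyses {20b} says that "Intervention effects will be analyzed in subgroups in multivariate analyses based on a limited set of clinicopathologic factors". Every factor it lists is divided in two:

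- age, below 75 versus 75 and over, for all outcomes;
- MoCA, below 26 versus 26 and over, for cognitive outcomes;
- incontinence, daily versus less than daily, for urinary outcomes;
- SPPB, below 10 versus 10 and over, for physical outcomes;
- PSQI, above 5 versus 5 or below, for sleep outcomes;
- GDS-15, 9 and over versus below 9, and GAD-7, 10 and over versus below 10, for depression and anxiety outcomes respectively.

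The age analysis will be done "unless this is precluded by a minimal subgroup sample size"; no such clause accompanies the other factors. Subgroup-specific effects are presented only when the treatment-by-subgroup interaction has p < 0.05. No interaction using the modifier on its recorded scale is stated, and no expected share on either side of any cut is given.

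The sample size section {14} concerns the main effect only. Its 270 women, in three equal arms, are meant "to detect an average treatment effect of 0.25 standard deviation’s difference in the composite cognitive function outcome over 6 months". Repeated measurements are taken to correlate at 0.75, and dropout to reach 15% at the end of treatment.

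**The concern.** Age is known in years, MoCA, SPPB, PSQI, GDS-15 and GAD-7 as scores, and incontinence as a count from a 7-day diary. Splitting such a variable discards all variation within each half. Eligibility admits MoCA scores from 18 upwards, so the split treats 18 and 25 as the same while separating 25 from 26. Whether women with lower cognition or higher age are more sensitive to the anticholinergic is close to the question that motivates the trial.

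The reporting rule raises the stakes. Because subgroup effects appear only when the interaction is significant, avoidable loss of power in that test removes results from view.

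The mood cuts raise a second issue. Nothing in the eligibility criteria selects for depression or anxiety, and randomisation is stratified by site alone. The upper groups could therefore be small, and the small-subgroup clause does not cover them.

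**Working it through.** **1. The plan's own figure.** Inputs from the sample size section: 90 women per arm, correlation 0.75, difference 0.25 SD, 15% loss by 6 months, 5% two-sided shared over two comparisons (0.025 each by Bonferroni, critical value 2.241). From the statistical methods section: the average of three visits, adjusted for baseline.

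- Variance factor: (1 + 2 × 0.75)/3 − 0.75² = 0.8333 − 0.5625 = 0.2708.
- No loss: SE = √(2 × 0.2708/90) = 0.0776; power = Φ(0.25/0.0776 − 2.241) = 84%.
- Loss building up to 15% by week 24 (retention 95%, 90%, 85% at the three visits, an assumed pattern): SE = 0.0808; power about 80.4%.

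The stated figure of more than 80% is reproduced. It covers the main effect, not any interaction. The SE of 0.0808 is carried forward.

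**2. Information kept after a cut.** Assume a normal modifier, an effect that changes linearly with it, and a share p beyond the cut. Relative to the test on the recorded scale, the two-group test keeps φ(z_p)²/[p(1 − p)]:

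| Share beyond cut | Kept | Lost |
|---|---|---|
| 50% | 64% | 36% |
| 25% | 54% | 46% |
| 20% | 49% | 51% |
| 10% | 34% | 66% |
| 5% | 22% | 78% |

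**3. What this does to power for the cognitive outcome.** Take an illustrative gradient in which the treatment effect changes by 0.2 SD per SD of the modifier, one treatment contrast, and two-sided 0.05.

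- Recorded scale: Φ(0.2/0.0808 − 1.96) = Φ(0.515) = 70%.
- 50:50 split: Φ(2.475 × √0.637 − 1.96) = Φ(0.015) = 51%.
- 25:75 split: Φ(2.475 × √0.539 − 1.96) = Φ(−0.143) = 44%.

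The document does not give the gradient or the split shares; both are assumptions.

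**4. The depression and anxiety cuts.** The share above each cut is not given, so a range is assumed:

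| Share above cut | Women per arm (of 90) | After 15% loss | Lost, normal score | Lost, exponential score |
|---|---|---|---|---|
| 20% | 18.0 | 15.3 | 51% | 35% |
| 10% | 9.0 | 7.6 | 66% | 41% |
| 5% | 4.5 | 3.8 | 78% | 53% |

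The last column uses p(ln p)²/(1 − p) for the information kept by a right-skewed score; at 5% this is 0.05 × 2.996²/0.95 = 0.47. If high scores are rare, skew is the more plausible shape, so the smaller losses are the better guide. At 5%, the binomial chance that a given arm of 90 has three or fewer such women is 34%.

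The SE of a two-group interaction, relative to the main effect, is 1/√[p(1 − p)]: 2.0 at 50%, 2.5 at 20%, 3.3 at 10% and 4.6 at 5%. No absolute detectable difference is given for the mood outcomes, because the correlation of 0.75 is stated for the cognitive outcomes only.

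**The case against.** The strongest defence is that these are secondary, exploratory analyses in a trial sized for main effects. Splitting a baseline modifier does not bias the randomised comparison or inflate type I error, and fixing the cuts in advance prevents a data-driven choice of threshold. The cuts also match status questions that matter in counselling, such as normal versus mildly impaired cognition. If modification really is a step at the cut, nothing is lost. The list does not forbid a supplementary continuous test, and the SAP is not shown.

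Much of this stands. It limits the point to efficiency and makes the loss conditional on graded modification. It does not remove the point: the article itself fixes the cuts and ties presentation to the interaction test, and it gives no reason to expect a step at any of them.

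Three stronger readings are tempting and are not supported.

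- A reader might infer that the depression and anxiety comparisons cannot inform. The document gives no share above either cut, and its background section associates urgency incontinence with depression. At 20%, 18 women per arm is not a handful.
- A reader might apply the normal-score losses of 66% to 78% to the mood scores. Those scores are bounded and, if high values are rare, skewed, which gives losses nearer 41% to 53% at the same shares.
- A reader might think that a curvature term settles the linearity assumption. In a sparse tail it has little power, and a continuous term adds no women there; it borrows from lower scorers.

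**Conclusion.** The point holds as a matter of efficiency in the planned effect-modification tests. All seven modifiers are tested only between two groups, although finer values are recorded. Under a normal modifier and a linear gradient, the loss is about 36% to 46% of the information for splits of 50% to 25%. In the cognitive illustration this takes power from about 70% to between 51% and 44%.

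For GDS-15 and GAD-7 the size is uncertain. Over assumed shares of 5% to 20%, the loss runs from 35% to 53% for an exponential score and up to 78% for a normal one. These comparisons may be uninformative, but the document does not establish that they will be. The small-subgroup clause covers age only.

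A reader might also infer a threat to the trial's main conclusion. There is none: the primary analysis does not use these subgroups.

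**What to change.** In the additional analyses section {20b}, make the interaction test use the modifier on its recorded scale: age in years; MoCA, SPPB, PSQI, GDS-15 and GAD-7 as scores; baseline incontinence as episodes per week, suitably transformed. Add a curvature term as a sensitivity check. Keep the existing cut-offs for display, giving treatment effects with confidence intervals at values within the observed range on each side. Extend the small-subgroup clause to all modifiers.

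The cost is wording and a little more analysis, with no new data. The secondary models are already adjusted for the baseline value of the outcome, so for PSQI, GDS-15, GAD-7 and incontinence frequency as outcomes the modifier is already in the model. The change should be made before unblinding, which the article places after database lock. The small downside is an assumed smooth gradient, which the curvature check can assess only in part where few women score high.
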